### Randomization and blinding

2.4

Eligible patients will be approached during their routine gastroenterology unit visit by the research team for recruitment. A single independent staff member will prepare the randomization sequence, which will be accomplished using a block design and a block size of 4. Randomization of a block will be done by means of a random-number chart. This study is an open-label trial due to the difference in administration method for each arm. The modified quadruple therapy group will have amoxicillin twice a day, whereas the bismuth-containing quadruple therapy group will have tetracycline 4 times a day. Therefore, doctors and participants will be aware of the drugs that are prescribed. However, only the rate of eradication success, adverse events, and compliance with the therapies will be considered outcomes of this trial, and it is believed that an open-label design in itself will not influence the procedure or results of the trial.

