### Statistical analysis

2.6

The sample size was calculated by using an α-error <0.05 and a β-error <0.2 for a 2-tailed significance test. The calculated number of subjects required for the trial is 100 in each arm, which was determined by assuming an eradication rate of 96.2% from treatment with bismuth-containing quadruple therapy for 14 days as seen in a previous study in Korea (per-protocol (PP) analysis), an equivalence margin of 8%, and a dropout rate of 10%.^[24]^

For the intention-to-treat (ITT) analysis, all participants who take at least the 1st dose of prescribed medications will be included and assessed and for the modified ITT analysis, all participants who take at least the 1st dose of prescribed medications and who are in the posttreatment *H pylori* status will be included and assessed. For the PP analysis, only those who maintain and complete treatment with the prescribed medications without violating the regulations (violation is <80% medication compliance; poor adherence to medication is defined as taking less than 80% of what is prescribed) will be included and assessed (Fig. 1).

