A recent study in Korea has shown that modified quadruple therapy has rates of eradication success and adverse events comparable to those of concomitant therapy.^[19]^ Characterizing the regional antibiotic resistance profile is important for *H pylori* eradication because antibiotic resistance is the chief cause of treatment failure. However, the study above did not explore antibiotic resistance profiles, making it difficult to interpret its results. A previous study has also shown that modified quadruple therapy is comparable to bismuth-containing quadruple therapy as a rescue regimen for patients with at least 2 consecutive treatment failures.^[20]^ Additionally, modified quadruple therapy has been shown to have high eradication success even in subjects with amoxicillin, metronidazole, or clarithromycin resistance, and this therapy has fewer adverse events and higher compliance than does bismuth-containing quadruple therapy.^[20]^

This study will compare the efficacy and safety of modified quadruple therapy and bismuth-containing quadruple therapy as well as presenting the phenotypic and genotypic antibiotic resistance profile of *H pylori*. The strength of this study resides in providing evidence regarding the efficacy and safety of using modified quadruple therapy as a 1st-line regimen in different regions of Korea compared to previous reports (a previous study was conducted in Seoul as a single center study; however, we will recruit patients in Gangwon and Gyeonggi provinces) and additionally, in providing evidence on the use of bismuth-containing quadruple therapy as a 1st-line treatment, which has been scarce as a 1st-line treatment in Korea. Moreover, with the comparative results of the antibiotic-susceptibility gold standard ‘agar dilution’ method vs. DNA sequencing of the clarithromycin resistance point mutations in the 23S rRNA of *H pylori*, it will be possible to interpret the outcome of this study in light of the antibiotic resistance profiles of *H pylori* including the unknown clinical significance of point mutations, such as G2141A, A2144T, or T2182C.

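### The set called ITT is a treated set: no stated analysis keeps all participants as randomised, in a trial where participants know their allocation

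*Protocol article*

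**What the plan says.** Section 2.6 (Statistical analysis) defines three sets:

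- **ITT:** "For the intention-to-treat (ITT) analysis, all participants who take at least the 1st dose of prescribed medications will be included and assessed".
- **Modified ITT:** "all participants who take at least the 1st dose of prescribed medications and who are in the posttreatment" *H pylori* status group, that is, dosed and with a known outcome.
- **Per-protocol:** "only those who maintain and complete treatment with the prescribed medications without violating the regulations", where a violation is compliance below 80%.

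The same section runs the comparisons of eradication, compliance and adverse events on these three sets.

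Section 2.4 (Randomization and blinding) explains why the trial is open-label: "The modified quadruple therapy group will have amoxicillin twice a day, whereas the bismuth-containing quadruple therapy group will have tetracycline 4 times a day". It accepts that "doctors and participants will be aware of the drugs that are prescribed", and then states that "it is believed that an open-label design in itself will not influence the procedure or results of the trial". Section 2.8 (Ethics) lets participants withdraw for any reason, with the reasons identified for reporting.

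**The concern.** Intention-to-treat keeps every randomised participant in the assigned arm, so that the groups compared are those that chance formed. A first-dose requirement removes people after randomisation. That can be harmless where allocation is concealed from the participant until dosing, because not starting then cannot depend on the arm. Here it can, because participants and doctors know the assigned drugs.

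The other two sets do not help. Each adds a condition to having been dosed, so agreement among the three analyses cannot reveal a problem that all three share. The compliance comparison is affected too, since people who take nothing are the extreme of non-compliance and are left out.

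This is not a detail deferred to a statistical analysis plan. The article states the definition outright.

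**Working it through.** **Inputs from Section 2.6.** Eradication 96.2% (per-protocol, bismuth-containing quadruple therapy), margin 8%, dropout 10%, two-tailed α 0.05, power 80%, 100 per arm.

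**Assumptions, not in the documents.** The same 96.2% among dosed participants in both arms; never-dosed participants counted as not eradicated; 0 to 5 non-starters per 100; Wald 95% intervals.

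**Step 1: the plan's own figure.** With equal rates and 0.025 per side,

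n = 2 × 0.962 × 0.038 × (1.960 + 0.842)² / 0.08² ≈ 89.7, so 90 per arm, and 90 / 0.90 = 100.

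The stated 100 per arm is reproduced. Changing the analysis set leaves it as it is.

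**Step 2: shift per non-starter.** If k of 100 in one arm never start, that arm's all-randomised rate is 96.2 × (1 − k/100). Each non-starter therefore costs 96.2 / 100 = 0.96 points. For k = 5 the rate is 0.95 × 96.2 = 91.4%, the shift is 96.2 − 91.4 = 4.8 points, and 4.8 / 8 = 60% of the margin.

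**Step 3: the two sets side by side.** Differences are modified minus bismuth-containing quadruple therapy, in percentage points. The standard error is √(p₁(1−p₁)/n₁ + p₂(1−p₂)/n₂), with n = 100 per arm for the all-randomised set and 100 − k for the dosed-only set.

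| Non-starters per 100, modified / bismuth-containing | Dosed-only difference (95% CI) | All-randomised difference (95% CI) |
|---|---|---|
| 0 / 0 | 0 (±5.3) | 0.0 (−5.3 to +5.3) |
| 1 / 1 | 0 (±5.3) | 0.0 (−5.9 to +5.9) |
| 0 / 2 | 0 (±5.3) | +1.9 (−4.0 to +7.8) |
| 0 / 3 | 0 (±5.3) | +2.9 (−3.3 to +9.1) |
| 0 / 5 | 0 (±5.4) | +4.8 (−1.8 to +11.5) |
| 5 / 0 | 0 (±5.4) | −4.8 (−11.5 to +1.8) |

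Example for 0 / 3: the bismuth-containing arm has 0.97 × 96.2 = 93.3%, and the difference is 96.2 − 93.3 = 2.9. The standard error is √(0.962 × 0.038/100 + 0.933 × 0.067/100) ≈ 3.15 points, so the interval is 2.9 ± 6.2. By symmetry, 3 / 0 gives −2.9 (−9.1 to +3.3).

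**Step 4: direction.** The dosed-only difference stays at 0 throughout. Refusals in the tetracycline arm raise the comparator's reported rate above its all-randomised rate, which flatters the comparator. Refusals in the modified arm flatter the modified regimen.

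**The case against.** The strongest reply is that few people who consent to a 14-day course fail to take a single dose, and that nothing in the documents shows refusal to depend on the arm. Much of this stands. Section 2.8 provides for consent after explanation and time for discussion, so some reluctant people will decline before randomisation. If nearly everyone takes a first dose, or if non-starting is balanced, the effect is small or nil.

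Four stronger readings may tempt a reader, and the documents do not support them.

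- **That the four-times-daily arm will drive people away.** Section 2.1 gives bismuth four times daily and metronidazole three times daily in both arms. Only the amoxicillin and tetracycline schedules differ.
- **That the protocol expects the arms to differ in starting treatment.** The Discussion says of modified therapy that "this therapy has fewer adverse events and higher compliance than does bismuth-containing quadruple therapy", but it is reporting an earlier study of rescue treatment after at least two failures. Side effects, and the poor compliance that they cause, come after the first dose, so those patients remain in the stated ITT set.
- **That non-starters vanish from the trial report.** Reasons for withdrawal are to be identified for reporting, and the flow chart in Figure 1 is not shown. They leave the comparison, not necessarily the report.
- **That the stated set always makes the conclusion easier to reach.** The sample size matches a non-inferiority formula. On that reading, refusals in the tetracycline arm make the stated set the stricter one: for 0 / 5 the lower limit is about −5.4 dosed-only and −1.8 all-randomised. The upper limit of 9.1 for 0 / 3 breaches the margin only if the margin is two-sided, which the term equivalence margin allows.

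None of this repairs the definition. The set is not intention-to-treat, and no other stated set fills the gap.

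**Conclusion.** The point holds as a mislabelled analysis set with a possible bias of unknown size and direction. That no stated analysis is all-randomised follows directly from the text. That non-starting can depend on allocation follows from the open-label design; that it will do so is not shown.

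The size rests on assumed non-starter numbers, equal eradication among dosed patients, and non-starters counted as failures. The figure of 60% of the margin is the extreme of that assumed range, five in one arm and none in the other, and should not be quoted as an expected effect. Even so, a net imbalance of three per 100 is enough to take one confidence limit past 8 points while the dosed-only interval stays within about ±5.4. The definition should be fixed, but the documents do not show that the trial's conclusion is in danger.

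**What to change.** In Section 2.6, define ITT as all randomised participants analysed in their assigned arm, with anyone lacking a post-treatment breath test, including the never-dosed, counted as not eradicated. The counting rule needs stating with the definition, because never-dosed participants will often have no test result. Rename the at-least-one-dose set the treated/safety set and use it for adverse events. Keep modified ITT and per-protocol as supportive sets, and bring Figure 1 into line if it shows the old definition. Settle this before outcomes are examined.

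The cost is small. The number randomised, the treatments and the visits do not change. ITT eradication rates may be slightly lower. Never-dosed participants must be kept in the analysis dataset, which means recording them as such; the protocol checks compliance only at the first visit, about two weeks after enrolment.

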**Figure 1 F1:**
[figure not shown]
Flow chart of the study. ITT = intention-to-treat, n = number, PP = per-protocol.

Continuous variables will be expressed as the mean ± standard deviation. Categorical variables will be expressed as numbers and percentages. First, we will compare the baseline characteristics of enrolled subjects (age, sex, smoking, alcohol use, reason for *H pylori* eradication) using Student *t* test and Fisher exact test for continuous and categorical variables, respectively. The Mann–Whitney test will be alternatively used if a continuous variable does not have a normal distribution. We will then perform ITT, modified ITT, and PP analyses to compare the eradication success rates, compliance with therapies, and adverse event rate between the 2 arms. Subgroup analyses will be performed according to the reason for eradication and the antibiotic resistance profile of the *H pylori* isolate. A *P* value <.05 (2-tailed) will be adopted as the threshold for statistical significance for all tests. All of the analyses will be performed using SPSS version 24.0. (SPSS Inc., Chicago, IL).

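### Section 2.6 tests three unranked outcomes in three analysis sets, each at P<.05, and does not carry over the one deciding contrast that the sample size implies

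*Protocol article*

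**What the plan says.** Section 2.4 (Randomization and blinding) of the protocol article gives a closed list: "only the rate of eradication success, adverse events, and compliance with the therapies will be considered outcomes of this trial". None of the three is ranked above the others.

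Section 2.6 (Statistical analysis) defines ITT, modified ITT and PP sets and then states: "We will then perform ITT, modified ITT, and PP analyses to compare the eradication success rates, compliance with therapies, and adverse event rate between the" two regimens. The threshold follows: "A *P* value <.05 (2-tailed) will be adopted as the threshold for statistical significance for all tests". Subgroup analyses by reason for eradication and by resistance profile come under the same rule.

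The only pointer to a deciding contrast is the sample-size paragraph of section 2.6. It gives the error rates ("The sample size was calculated by using an α-error <0.05 and a β-error <0.2 for a 2-tailed significance test") and rests on this premise: "assuming an eradication rate of 96.2% from treatment with bismuth-containing quadruple therapy for 14 days". The rate is taken from the per-protocol results of an earlier Korean study. The other inputs are an equivalence margin of 8% and 10% dropout, giving 100 per arm. The margin does not appear again in the analysis text, and no sentence names a primary outcome, a deciding set or a rule for when the sets disagree.

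**The concern.** The sample-size paragraph and the analysis paragraph describe different trials. The first is built on one outcome, one set and a margin. The second makes three outcomes by three sets, nine comparisons, each judged by a two-tailed P value. At most eight of them are informative if compliance is compared as the proportion reaching 80%, because PP excludes everyone below that level.

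Two things are at stake. First, for eradication, ITT and PP can lead to different conclusions on the same data. In an open-label trial with no deciding set named, that choice could be made after the results are known. Second, if all three outcomes were treated as confirmatory, the chance of at least one false claim of a difference would exceed the 5% that the reader takes from the text.

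**Working it through.** **1. Reproduce the stated sample size.** Inputs from section 2.6: 96.2% for the bismuth-containing arm, margin 8 points, 80% power, two-tailed alpha 0.05, dropout 10%. Assumption: the same rate in the modified arm.

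n = 2 × 0.962 × 0.038 × (1.960 + 0.842)² / 0.08² = 89.7, rounded up to 90. Then 90 / 0.9 = 100 per arm, as stated.

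This matches a 95% confidence interval judged on one side against the margin (one-sided 0.025). Two one-sided tests at 0.05 would need 98, then 109 after dropout. A superiority test of 96.2% versus 88.2% would need 176, then 196. So the 100 per arm belongs to eradication, at a PP rate, against the margin.

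**2. What each set shows when the arms are identical.** Assumptions, none of them stated in the article: all 10% dropouts are untested, they leave PP, and they count as failures in ITT.

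| | PP | ITT |
|---|---|---|
| Cure rate | 96.2% | 0.962 × 0.9 = 86.6% |
| n per arm | 90 | 100 |
| Standard error, √(2p(1−p)/n) | 2.85 points | 4.82 points |
| 95% CI half-width, 1.96 × SE | 5.6 points | 9.4 points |
| Power, Φ(8/SE − 1.96) | Φ(0.85) = 80% | Φ(−0.30) = 38% |

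With equal observed rates, the PP interval lies inside the 8-point margin and the ITT interval does not.

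**3. How often the sets disagree.** Simulation of 400,000 trials: 100 per arm, each patient tested with probability 0.9, each tested patient cured with probability 0.962. Success means that the lower 95% Wald limit for modified minus bismuth-containing therapy lies above −8 points.

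- PP succeeds: 80%
- ITT succeeds: 39%
- Both succeed: 37%
- PP only: 80 − 37 = 43%
- ITT only: 39 − 37 = 2%
- Disagreement: 43 + 2 = 45%

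**4. False-positive chance if every comparison were a confirmatory difference test.** The article gives no correlations, so these are ranges.

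- Three outcomes in one set: 1 − 0.95³ = 14.3% if independent, 12.5% at correlation 0.5, 9.8% at 0.8.
- Three independent outcomes in three sets: 14.3% if the sets agree fully (correlation 1), 23.0% at 0.9, 26.6% at 0.8, 29.3% at 0.7.
- Outer bound, nine independent tests: 1 − 0.95⁹ = 37.0%.
- Patient-level null simulation of the eight informative comparisons, 100 per arm (assumed dropout 5–10%, adequate compliance 90–95%, adverse events 30–50%): 14–16% with Fisher tests and 21–23% with chi-square tests. Between-set correlations there were about 0.46–0.85 for eradication and 0.90–0.97 for adverse events, so one common correlation is only a rough summary.

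**The case against.** The strongest reply is that this is a condensed article. Ranking of outcomes, the deciding set and multiplicity rules are often left to a full protocol or SAP, and the list in section 2.4 serves to argue that open-label treatment does little harm, not to set a hierarchy. This carries weight, but section 2.6 does more than stay silent: it fixes one threshold for all tests across all outcomes and sets. An SAP that confined P<.05 to one contrast would depart from that sentence.

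A reader might infer that nothing in the plan identifies what decides the trial, or that any of the nine comparisons may be presented as its result. The document does not support either. The sample size points to eradication in PP and reproduces exactly on that basis, and the analysis text says only that the comparisons will be made.

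A reader might also put the false-positive rate at 15–29%, or at three or more times the nominal level. That is too strong. The figure depends on unstated correlations. Three outcomes in one set give 9.8–14.3%, which is 2.0 to 2.9 times 5%. ITT, modified ITT and PP examine one hypothesis in overlapping patients, so they are not separate claims. These rates also count false differences, whereas the error that matters for a margin is a false conclusion of equivalence.

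Finally, the disagreement in step 3 rests on handling rules that the article does not state. Its PP definition spells out only compliance below 80% as a violation, with no breath-test requirement. Part of the 45% simply reflects low ITT power. Both points stand, so the figure is conditional. They do not remove the need to say which set decides.

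**Conclusion.** The point holds as a mismatch within section 2.6. The sizing implies one deciding contrast, and the analysis text replaces it with unranked comparisons at a common threshold.

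The main consequence concerns eradication. With 96.2% cure in both arms, and with all 10% dropouts untested, leaving PP and counted as ITT failures, PP meets the margin in about 80% of trials and ITT in about 39%, and they disagree in about 45%.

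Multiplicity is secondary and less certain. If all three outcomes were read as confirmatory, the chance of at least one false difference would be about 10–14% in one set. Over three sets it would be about 14–29%, given independent outcomes and between-set correlation of 0.7–1, and about 15% in the patient-level simulation with Fisher tests. None of these figures measures false equivalence.

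**What to change.** In section 2.6 or the SAP, before database lock:

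- Name eradication success, modified versus bismuth-containing quadruple therapy, judged against the 8% margin, as the single primary contrast.
- Name the set that decides. PP is the set on which the 100 per arm was sized. Report the other sets as supportive.
- Replace the all-tests threshold with a confirmatory level for the primary contrast only. Report adverse events and compliance as secondary estimates with 95% confidence intervals.

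This takes a few sentences and no extra patients or data. The cost is that a difference in adverse events or compliance can no longer be claimed as confirmatory.

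Requiring success in both ITT and PP is a legitimate alternative and needs no alpha adjustment, but it is a real trade-off. Under the assumptions above, the stated 80% power would have to be restated as about 37%, and ITT alone would need 285 per arm for 80% power.

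### Compliance and adverse events are also to be compared in the per-protocol set, which is itself selected on completing treatment with at least 80% compliance

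*Protocol article*

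**What the plan says.** Section 2.4 (Randomization and blinding) states that "only the rate of eradication success, adverse events, and compliance with the therapies will be considered outcomes of this trial". Compliance and adverse events are thus two of the three declared outcomes.

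Section 2.6 (Statistical analysis) defines three analysis sets:

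- **ITT:** everyone who took at least one dose of study medication.
- **Modified ITT:** the same participants, limited to those "who are in the posttreatment *H pylori* status will be included and assessed". I read this as having a known post-treatment result. No compliance condition is attached.
- **PP:** "only those who maintain and complete treatment with the prescribed medications without violating the regulations", with the rule spelled out as "violation is <80% medication compliance; poor adherence to medication is defined as taking less than 80% of what is prescribed".

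The same section then says that the investigators will "perform ITT, modified ITT, and PP analyses to compare the eradication success rates, compliance with therapies, and adverse event rate between the 2 arms". It sets a two-tailed P below .05 as the threshold for all tests. It does not say which of the three sets decides for compliance or for adverse events.

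**The concern.** An outcome should not be compared in a set chosen on that outcome. Compliance of at least 80% is a condition of entry to PP, so PP cannot show whether the regimens differ in the share of patients who comply adequately.

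Adverse events have a related problem. Side effects are a reason to stop treatment or to miss doses, and participants who do so leave PP. The PP adverse-event rate is therefore a rate among those who tolerated the drugs well enough to finish them. If the regimens differ in how many people they drive off treatment, PP removes different fractions of the two randomized arms and the comparison no longer rests on randomization.

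What is at stake is the reading of two declared outcomes. Each can yield up to three results, all judged at the same threshold. A PP finding of no difference in compliance carries no information, yet could be reported as support for similar compliance. A PP finding on adverse events could be set beside the ITT finding as if it had equal standing.

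**Working it through.** The plan gives no figure on this point to reproduce. The check is of definitions, followed by an illustration.

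**Step 1: compliance in PP.** Entry to PP requires compliance of at least 80%. Adequate compliance is the complement of poor adherence, which the plan also places at 80%. So, among PP participants:

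- share with adequate compliance = 100% in each arm; difference = 0, whatever happened in the trial;
- compliance as a continuous percentage is confined to 80–100%. A difference can still appear, but only in what remains after the low values are cut off.

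**Step 2: adverse events in PP.** Let *a* be the proportion of an arm with an adverse event, and *s* the proportion who stop or fall below 80% because of one. Assume that everyone in *s* leaves PP and nobody else does. Then

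PP rate = (*a* − *s*) / (1 − *s*).

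This is below *a* whenever *s* > 0 and *a* < 1, so PP understates the rate in any arm with such participants.

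The documents give no adverse-event or stopping rates. The following inputs are assumptions: true rates of 40% in one arm and 50% in the other, a difference of 10 points.

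| Stopping (40% arm / 50% arm) | PP rate, 40% arm | PP rate, 50% arm | PP difference |
|---|---|---|---|
| 0% / 5% | 0.40/1.00 = 40.0% | 0.45/0.95 = 47.4% | 7.4 points |
| 2% / 10% | 0.38/0.98 = 38.8% | 0.40/0.90 = 44.4% | 5.7 points |
| 5% / 15% | 0.35/0.95 = 36.8% | 0.35/0.85 = 41.2% | 4.3 points |
| 5% / 5% | 0.35/0.95 = 36.8% | 0.45/0.95 = 47.4% | 10.5 points |

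The difference shrinks in the three rows where more people stop in the arm with more events. With equal stopping it does not shrink, although both rates are still too low.

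**Step 3: the other two sets.** ITT requires one dose and nothing more, so those who stop remain and the rates are the true 40% and 50%. In modified ITT, a participant who stops for side effects but has the follow-up breath test also remains. Only those without a post-treatment result are lost. Section 2.3 schedules that test at the second visit and states no rule that excludes early stoppers from it.

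**The case against.** The strongest reply is that the same sentence also plans the ITT comparison, in exactly the set one would choose for safety and compliance. That is correct. A reader might infer that the trial's safety comparison drops those who stopped for side effects, or that the plan hides a tolerability difference. The documents do not support either reading. The sound comparison is planned, and the fault lies in placing a void one and a selected one beside it.

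Four further points limit the concern:

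- **Modified ITT.** It would be wrong to extend the 80% argument to this set. Some early stoppers may miss the breath test, but nothing in the document shows how many.
- **Zero difference.** This holds only for compliance split at 80%. Section 2.6 does not say how compliance will be compared, and it provides methods for continuous variables.
- **Size.** Distortion of the adverse-event difference depends on unequal stopping, which is assumed.
- **Expected difference.** The Discussion says of the modified regimen that "this therapy has fewer adverse events and higher compliance than does bismuth-containing quadruple therapy". A reader might take this as the trial's own expectation. It reports a cited study of rescue treatment after at least two failures, whereas this trial is first-line. It makes unequal stopping plausible and no more.

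It can also be said that the order of the sets may be given in a full protocol or SAP that is not shown, and that adverse events in completers are a legitimate supplement. The first may be so, and the missing order alone would not be a finding. But the PP comparison of compliance is stated in this document, and no order of sets makes it informative. The second is fair for description, but less so for a between-arm test at P below .05 on the same footing as ITT.

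**Conclusion.** The point holds for the PP set. The PP comparison of adequate compliance is circular, and this follows from the definitions alone. PP adverse-event rates are conditioned on tolerating the drugs. They understate the rates wherever someone leaves PP because of side effects, and they can shrink or distort the arm difference if such losses are unequal. Under the assumed rates, a true 10 points becomes 4.3 to 7.4 points with more stopping in the worse arm and 10.5 points with equal stopping. These figures show the mechanism and do not forecast this trial.

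The ITT comparison is sound, modified ITT carries only a possible and indirect selection, and the eradication endpoint is not affected. This should be corrected, but it does not threaten the trial's main comparison.

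**What to change.** In section 2.6:

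- name the ITT set (at least one dose taken) as the set for comparing compliance and adverse events, with early stoppers kept in;
- drop the PP comparison of compliance and of adverse events;
- keep the modified ITT and PP analyses for eradication.

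The cost is a change of wording and fewer tests. No new data are needed. The 100 per arm rests on the assumed eradication rate, the margin and the dropout allowance, none of which is touched. The one loss is a supplementary description of adverse events among completers.

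### The 8-point equivalence margin that sizes the trial enters no stated analysis, and the only stated criterion, a 2-tailed P<.05, cannot show that the arms lie within it

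*Protocol article*

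**What the plan says.** All of this stands in section 2.6 (Statistical analysis) of the protocol article.

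- **Sizing.** The errors are "an α-error <0.05 and a β-error <0.2 for a 2-tailed significance test". The rate is set by "assuming an eradication rate of 96.2% from treatment with bismuth-containing quadruple therapy for 14 days", taken from a per-protocol analysis. The remaining inputs are "an equivalence margin of 8%, and a dropout rate of 10"%. The result: "The calculated number of subjects required for the trial is 100 in each arm".
- **Analysis.** After the baseline comparisons, the investigators will "perform ITT, modified ITT, and PP analyses to compare the eradication success rates, compliance with therapies, and adverse event rate between the 2 arms".
- **Criterion.** A P "value <.05 (2-tailed) will be adopted as the threshold for statistical significance for all tests".

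The margin appears only in the sizing sentence. No equivalence or non-inferiority hypothesis is stated, and no confidence interval is set against the 8 points. Fisher's exact test is named for categorical baseline characteristics; no test is named for eradication rates. No eradication rate is given for the modified regimen.

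**The concern.** The sizing and the analysis answer different questions. A margin-based size belongs to a trial that aims to show the new regimen is not worse than the comparator (or not different from it) by more than the margin. A 2-tailed P<.05 on a comparison of rates asks only whether the data rule out a zero difference. Failing to rule out zero does not rule out a loss of 8 points.

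The main efficacy conclusion is at stake. Under the stated criterion, a regimen that is worse by the full margin often produces no signal, and one that is truly as good has no stated way to be shown so. The wording also leaves open whether the design is two-sided equivalence or one-sided non-inferiority, and the two need different numbers of patients.

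**Working it through.** **Inputs (section 2.6):** comparator rate p = 0.962; margin m = 0.08; beta 0.2; dropout 10%; 100 per arm. **Assumption:** the modified arm also has p = 0.962 when sizing, because its rate is not given.

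**1. Reproducing 100 per arm.** For non-inferiority at one-sided 0.025 with 80% power:

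n = 2p(1-p)(1.960 + 0.842)² / m² = 0.0731 × 7.849 / 0.0064 = 89.7, so 90 evaluable; 90/0.9 = 100. This matches exactly.

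Other designs with the same inputs do not match:

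| Design | Evaluable per arm | After 10% dropout |
|---|---|---|
| Non-inferiority, one-sided 0.05 | 71 | 79 |
| Equivalence, two one-sided tests at 0.05 (90% CI) | 98 | 109 |
| Equivalence, two one-sided tests at 0.025 (95% CI) | 121 | 135 |
| Two-sided difference test, 96.2% vs 88.2% | 176 | 196 |

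So the size fits a non-inferiority test. It is about half of what a difference test would need to detect an 8-point loss.

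**2. What the P<.05 criterion does at this size.** Take 90 evaluable per arm, comparator 96.2%, and enumerate all outcomes of two independent binomials:

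| True deficit of modified arm | Fisher P≥.05 | Chi-square P≥.05 |
|---|---|---|
| 5 points (91.2%) | 81% | 73% |
| 8 points (88.2%) | 57% | 47% |
| 10 points (86.2%) | 40% | 31% |

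The normal approximation agrees: power to detect 96.2% vs 88.2% with 90 per arm is about 52%.

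**3. What a margin test does at the same size.** With a true 8-point deficit, the lower 95% limit lies above -8 points in about 3.4% of trials with a Wald interval and 2.5% with Newcombe.

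**4. The two criteria on one data set.** Suppose 81/90 (90.0%) on the modified regimen and 87/90 (96.7%) on the comparator. The difference is -6.7 points and Fisher P = 0.13. The Newcombe 95% CI is -14.9 to +0.9 points, so a loss well beyond 8 points is not excluded.

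The criteria also diverge when the arms are truly equal at 96.2%. A non-significant Fisher result together with a lower limit at or below -8 points occurs in about 21% of trials (Wald) or 30% (Newcombe).

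**5. Power of a margin test with 90 evaluable per arm, both arms at 96.2%.** SE = √(0.0731/90) = 0.0285, and m/SE = 2.807. Under the normal approximation:

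- Non-inferiority: Φ(2.807 - 1.960) = 80%.
- Equivalence with a 95% CI: 2 × 0.801 - 1 = 60%.
- Equivalence with a 90% CI: 2Φ(2.807 - 1.645) - 1 = 76%.

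Exact enumeration with 95% intervals:

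| Interval | Non-inferiority | Equivalence |
|---|---|---|
| Wald | 79% | 57% |
| Newcombe | 69% | 39% |

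**The case against.** A reader might infer that the investigators will report a non-significant P as proof that the regimens are comparable. The protocol does not say so. Its aim is neutral, to compare efficacy and safety; the statements that regimens were comparable, in the Introduction and Discussion, describe earlier studies. How P≥.05 would be read is unknown, and this point does not rest on it.

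Second, no test is named for eradication rates, and a general significance threshold is not itself a primary success criterion; non-inferiority tests also yield P values. This stands as a limit on the numbers: the 57% belongs to Fisher, and chi-square gives 47%. Nothing in section 2.6, however, ties any test to the margin.

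Third, this is a condensed article, and a fuller protocol or SAP may set out a margin test. The interval method could properly be left there. But the article does more than omit it: it labels the sizing a 2-tailed significance test, calls the margin an equivalence margin, gives a number that fits neither label, and applies one threshold to all tests. Those statements need reconciling whatever another document says.

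Lastly, the choice of primary set is debatable. The per-protocol set underlies the sizing, but it drops patients below 80% compliance in an open-label trial where compliance is itself an outcome. That argues for reporting both sets.

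**Conclusion.** The point holds as a mismatch within section 2.6: the trial is sized to test an 8-point margin, and no stated analysis tests it. The stated P<.05 criterion cannot support an equivalence or non-inferiority conclusion. At a true deficit equal to the margin it would be non-significant in about half of trials (47% to 57% by test), whereas a 95% interval judged against -8 points would wrongly pass about 3%.

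These figures assume 90 evaluable per arm, a true comparator rate of 96.2%, and a chi-square or Fisher test. The reproduction of 100 per arm further assumes equal rates in both arms. That match makes non-inferiority at one-sided 0.025 the likely basis of the size; the document does not confirm it. This should be corrected before analysis, because it governs the main efficacy conclusion.

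**What to change.** In section 2.6:

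1. State the primary efficacy analysis as the two-sided 95% CI for the difference in eradication rate, modified minus bismuth-containing quadruple therapy. Conclude non-inferiority only if the lower limit is above -8 points.
2. Name the interval method in advance. Failures are few, so the method matters.
3. Report the result in both the PP set, on which the size is built, and the ITT set.
4. State that P≥.05 is not evidence of equivalence, and keep the P<.05 threshold for the other comparisons.
5. In the sizing text, replace equivalence and the 2-tailed significance test with non-inferiority at one-sided 0.025, and state the rate assumed for the modified arm.

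**Cost.** For non-inferiority with the normal-approximation sizing, this is a change of wording plus one interval, and 100 per arm stands. The downside is that power depends on the interval: at 90 evaluable per arm, exact power is about 79% with Wald and 69% with Newcombe, so it should be restated for the method chosen. With Newcombe, about 120 evaluable per arm (120/0.9, so 134 randomised) would be needed to exceed 80%.

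If two-sided equivalence is what the sponsor means, wording alone is not enough. Power at 90 evaluable per arm must then be restated: by normal approximation about 60% with a 95% CI or 76% with a 90% CI; exactly, about 57% (Wald) or 39% (Newcombe) with a 95% CI. Keeping 80% power by the normal approximation would take 109 (90% CI) or 135 (95% CI) randomised per arm.
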